#### 7.4.2 Death Date

In the unlikely event that a patient’s death date is missing, the date of death will be assumed as described in this section in calculating the time to events (DFS, LFS, MFS or OS) in the efficacy analyses:

- - If the information of date of death is partially or completely missing, the patient will be censored at the last documented information obtained for living patient.

# EFFICACY VARIABLES

Events for LFS will mean CRF 20 OR 99 = Yes,

- Locoregional recurrence-free survival (LFS)

A patient’s locoregional survival time is defined as the time from surgery to the date of locoregional recurrence/death from any cause. In the case of patients who did not present a locoregional recurrence at the time of data-cut-off, the survival time will be censored.

| LFS (days) | = Date of locoregional  recurrence / Death/  Censoring | - Date of surgery + 1 |
| --- | --- | --- |
|  |  |  |

The censoring rules used in the calculation of LFS will be obtained from Table 1 below.

| **Table 1. Censoring rules used in the calculation of LFS** | | |
| --- | --- | --- |
| **Situation** | **End date** | **Censored** |
| Documented locoregional recurrence during the study | Date of the 1st assessment of the series of tests that determined locoregional recurrence | Noa |
| Death during the study before locoregional recurrence | Date of death | No |
| Locoregional recurrence documented between scheduled visits | Date of the 1st assessment of the series of tests that determined locoregional recurrence | No |
| Discontinued due to locoregional recurrence, but no documented locoregional recurrence. | Date of last tumor assessment before discontinuation. | Yes |
| No baseline assessments | Date of surgery | Yes |
| Death or locoregional recurrence after one or more missed scheduled assessments | Date of last tumor assessment | Yes |
| Patients still on treatment without PD as of data cut-off | Date of last tumor assessment | Yes |

a Earliest date among the dates used in calculating the progression-free survival.

- Disease-free survival (DFS)

A patient’s DFS is defined as the time from surgery to the date of disease recurrence/death from any cause. In the case of patients who did not present any event (i.e. those lost to FU or patients who did not have any recurrence at the time of data cut-off), DFS will be censored.

| DFS (days) | = Date of recurrence /  Death/ Censoring | – Date of surgery + 1 |
| --- | --- | --- |

The censoring rules used in the calculation of DFS will be obtained from Table 2 below.

| **Table 2. Censoring rules used in the calculation of DFS** | | |
| --- | --- | --- |
| **Situation** | **End date** | **Censored** |
| Documented recurrence during the study | Date of the 1st assessment of the series of tests that determined recurrence | Noa |
| Death during the study before recurrence | Date of death | No |
| Recurrence documented between scheduled visits | Date of the 1st assessment of the series of tests that determined recurrence | No |
| Discontinued due to recurrence, but no documented recurrence. | Date of last tumor assessment before discontinuation. | Yes |
| No baseline assessments | Date of surgery | Yes |
| Death or recurrence after one or more missed scheduled assessments | Date of last tumor assessment | Yes |
| Patients without recurrence as of data cut-off | Date of last tumor assessment | Yes |

a Earliest date among the dates used in calculating the progression-free survival.

How can this be found ? Using CRF 20, 30 OR 99 = Yes.

- Metastasis-free Survival (MFS)

A patient’s MFS is defined as the time from surgery to the date of metastasis occurence/death from any cause. In the case of patients who did not present an event (i.e. those lost to FU or patients who did not have any metastases at the time of data-cut-off), MFS will be censored.

| MFS (days) | = Date of metastasis /  Death/ Censoring | – Date of surgery + 1 |
| --- | --- | --- |

The censoring rules used in the calculation MFS will be obtained from Table 3 below.

| **Table 3. Censoring rules used in the calculation of MFS** | | |
| --- | --- | --- |
| **Situation** | **End date** | **Censored** |
| Documented metastases during the study | Date of the 1st assessment of the series of tests that determined metastases | Noa |
| Death during the study before metastases | Date of death | No |
| Metastases documented between scheduled visits | Date of the 1st assessment of the series of tests that determined metastases | No |
| Discontinued due to metastases, but no documented recurrence. | Date of last tumor assessment before discontinuation. | Yes |
| No baseline assessments | Date of surgery | Yes |
| Death or metastases after one or more missed scheduled assessments | Date of last tumor assessment | Yes |
| Patients without metastases as of data cut-off | Date of last tumor assessment | Yes |

a Earliest date among the dates used in calculating the progression-free survival.

How can this be found ? Using CRF30, 99 = Yes.

- Overall Survival (OS) (event: CRF 99 = Yes)

A patient’s survival time will be defined as the time from surgery to the date of death due to any cause. If the patient has not died, the survival time will be censored on the last date the patient was known to be alive.

| Overall Survival (days) | = Date of death / censoring | - Date of surgery + 1 |
| --- | --- | --- |

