# SAFETY VARIABLES

The safety variables include:

- - post-operative pain (CRF pain scales, post-operative pain medications and CRF16 chronic pain)
  - peri- and post-operative blood loss. (<note to programmer: CRF perioperative blood loss and CRF60)
  - Serious adverse events (note to programmer: CRF70)

Cardiac events (CRF40) and gastro-intestinal events (CRF50).

A Serious Adverse Event (SAE) is defined as any AE that results in death, is life threatening, requires inpatient hospitalization or prolongation of existing hospitalization, results in persistent or significant disability/incapacity, or is a congenital anomaly/birth defect. Drug relationship will be assessed as above.

SAEs will be considered only during the 30 days after the administration of the study product (single administration, first=last).

In the event that a partial Start Date (month/year or year) is available, and month/year or year occurs before that of first treatment dose, the AE is considered as non-treatment emergent. However, if month/year or year occurs on or after the date of first treatment dose, the following cases will be considered:

- if month/year is available and month/year of Start Date >= month/year of first treatment dose, the AE is treatment emergent and Start Date will be estimated as the first day of the month;
- if only year is available and year of Start Date >= year of first treatment dose, the AE is treatment emergent and Start Date will be estimated as Jan. 1 of that year.
- In the event that the Start Date is completely missing, Stop Date will be used to determine when the AE resolved. If the AE stopped before first treatment dose, the AE will be considered as non-treatment emergent; otherwise, if the AE stopped on or after first treatment dose or is ongoing, the AE will be considered as treatment emergent and the Start Date of the event will be estimated as first treatment dose.

The estimated start dates will not be listed.

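### Tables 1–3 censor patients who leave for suspected but undocumented recurrence in a single-dose trial, and the rows conflict if such a patient later relapses or dies

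*SAP*

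**What the plan says.** The rules are in the SAP under Efficacy Variables, Tables 1 to 3.

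- Table 2 (DFS) has the row "Discontinued due to recurrence, but no documented recurrence". The end date is "Date of last tumor assessment before discontinuation" and the patient is marked as censored.
- Table 1 (LFS) has the matching row "Discontinued due to locoregional recurrence, but no documented locoregional recurrence", and Table 3 (MFS) has "Discontinued due to metastases, but no documented recurrence", with the same end date and status.
- Table 1 closes with "Patients still on treatment without PD as of data cut-off". The closing rows of Tables 2 and 3 instead refer to patients without recurrence or without metastases at data cut-off.
- The footnotes to all three tables refer to progression-free survival, which is not an endpoint of this trial.
- The study drug is given once, at induction of anesthesia (sections 4.1 and 4.6). Safety Variables confirms this: "single administration, first=last".
- For OS, the rule is "If the patient has not died, the survival time will be censored on the last date the patient was known to be alive".

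The SAP does not define what a patient discontinues, and it gives no order of precedence among the rows.

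**The concern.** These rows suit a trial in which patients stay on a drug until progression. Here nobody is on study drug during follow-up, so stopping it cannot help to define an endpoint. If discontinuing means leaving follow-up instead, the row can apply, but then patients are censored because someone suspected the very event being counted. The Kaplan-Meier estimate and the log-rank test (sections 10.9.1 and 10.9.2) assume that censored patients have the same outlook as those who remain at risk. These patients probably do not.

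The second difficulty is what happens afterwards. The same later death or documented recurrence can be an event or a censored observation depending on which row the programmer reads first. This affects the primary endpoint, and sections 10.9.1 and 10.9.2 plan no sensitivity analysis that would show the consequence. The per-protocol repeat does not address it.

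**Working it through.** The plan gives no figure on this point to reproduce. The check has two parts.

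**1. The passages side by side.** Take a patient with a clear assessment at 1 year who leaves before the 2-year visit because recurrence is suspected but not documented, and who dies after the 2-year visit was due.

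| Source in the SAP | DFS result |
| --- | --- |
| Table 2, discontinuation row | Censored at the 1-year assessment |
| Table 2, row for an event that follows a missed visit | Censored at the 1-year assessment |
| DFS definition (recurrence, or death of any cause) | Event at death |
| Table 2, row for death before recurrence | Event at death |
| Programming note (CRF 20, 30 or 99 answered yes) | Event |
| OS definition | OS event at death |

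If the death came before the 2-year visit was due, the missed-visit row would drop out, but the discontinuation row would still oppose the death row. If the patient instead had a recurrence documented after leaving, the documented-recurrence row and the programming note give an event. The missed-visit row censors it, and so does the discontinuation row if lack of documentation is judged at departure, which the SAP does not specify. Because assessments are only required at least yearly (section 7.3), the censoring date can lie about a year before departure.

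In Table 1, the last row fits nobody in a single-dose trial. The LFS text says that patients without locoregional recurrence at cut-off are censored but gives no date. A patient with distant metastases only therefore has no clear end-date rule.

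**2. Possible size.** The SAP gives neither a withdrawal rate nor a control event rate, so all rates here are assumptions.

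*Precision.* With equal allocation SE(log HR) ≈ 2/√d for d events, so losing k events multiplies the SE by √(d/(d − k)). For an assumed 40 to 60 events and 2 to 5 lost, the extremes are √(60/58) = 1.017 and √(40/35) = 1.069, an SE 1.7% to 6.9% wider.

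*Simulation.* 100 patients per arm (200 at 1:1, section 4.5), exponential times, HR 0.67 (the 33% reduction in section 4.5 read as a hazard ratio), 2-year follow-up, yearly visits, two-sided 5% log-rank test, 2,000 runs per scenario. A share of failures is treated as undocumented departures, censored at the last visit, with no later event recorded. Equal shares in both arms:

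| Two-year control event rate | Share lost | Mean events | Control DFS at 2 years | HR | Power |
| --- | --- | --- | --- | --- | --- |
| 30% | 0 | 51.3 | 70.0% | 0.668 | 30.4% |
| 30% | 5% | 48.6 | 71.1% | 0.667 | 28.9% |
| 30% | 20% | 40.9 | 74.8% | 0.666 | 24.1% |
| 50% | 0 | 87.1 | 50.2% | 0.675 | 44.0% |
| 50% | 5% | 83.0 | 51.4% | 0.670 | 44.5% |
| 50% | 20% | 69.9 | 56.4% | 0.663 | 40.5% |

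Control DFS rises by 1.1 to 6.2 points. At a 20% loss, power falls by about 4 to 6 points in the simulation and by 5 to 8 points by the Schoenfeld formula (29.9% to 24.9%, and 46.4% to 38.7%).

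*Unequal shares.* Roughly, observed HR ≈ true HR × (1 − share lost on ketorolac)/(1 − share lost on placebo). With 15% lost on ketorolac and 5% on placebo, 0.67 × 0.85/0.95 = 0.60; reversed, 0.67 × 0.95/0.85 = 0.75. The simulation gives 0.61 and 0.74 to 0.75. At a true HR of 1.0 it gives 0.90 to 0.91 and 1.10, with type I error of about 6% to 8%, against 5.4% to 5.6% in the same simulation without loss.

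**The case against.** The strongest reply is that the row concerns undocumented recurrence only. A documented recurrence is an event, at or between scheduled visits, and requiring documentation is a common and defensible endpoint choice. That stands: a reader might infer that everyone who leaves because of recurrence is censored, and the tables do not say so.

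Next, the row may apply to few patients or none. If it refers to study drug, a single dose leaves it empty. Nothing in the SAP says that recurrence ends participation, and the 1-, 2- and 5-year visits are scheduled without that condition. An investigator who suspects recurrence may also record it on the forms named in the programming note, which would make it an event. The size is therefore unknown, but the conflict between rows remains.

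A reader might also infer that later deaths are certainly lost from DFS. That is one of two readings, since the definition, the death row and the programming note all count them. What is certain is only that precedence is undefined.

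Finally, a reader might infer that an effective drug would itself bias the hazard ratio, because fewer ketorolac patients would leave with suspected recurrence. It would not. Removing 10% of events from each arm turns 20 versus 30 into 18 versus 27, and both crude ratios are 0.67. Bias needs different shares, which double blinding makes less likely.

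The Table 3 wording (recurrence where metastases is evidently meant) changes almost nothing: a patient who falls outside that row reaches the closing row and is censored at the last tumor assessment anyway.

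**Conclusion.** The concern holds in a limited form. Tables 1 to 3 censor patients whose reason for leaving is the suspected but undocumented endpoint. For a later documented event or death they contradict the endpoint definitions without saying which rule prevails. OS itself is unaffected, so the same patient could be an OS event and censored for DFS.

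The likely effects are some lost events and DFS, LFS and MFS curves that are somewhat too high. For DFS in the control arm this is about 1 to 6 points at two years if 5% to 20% of failures are caught and the control event rate is 30% to 50%. Those inputs are assumptions, and the number of patients affected cannot be derived from the SAP. The hazard ratio is biased only if the lost share differs between arms, and the direction is unknown. The documents do not support a claim of bias for or against ketorolac. The rule should still be corrected, because two programmers could derive different primary endpoint data from the present text.

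**What to change.** - State that DFS, LFS and MFS do not depend on discontinuation. Any documented recurrence or metastasis that the endpoint counts, and any death, known from any source within the limits of consent, is an event on its date. This takes precedence over both the discontinuation row and the missed-visit row.
- Delete the discontinuation rows from Tables 1 to 3, or limit them to patients with no later documented event or death.
- Add a sensitivity analysis that counts undocumented recurrences judged present by the investigator as events on the date of that judgement. Keeping documented events as primary leaves the documentation requirement intact.
- Replace Table 1's last row with one for patients free of locoregional recurrence and alive at data cut-off, whether or not they have distant metastases, using the same end date as the closing rows of Tables 2 and 3.
- If the discontinuation row in Table 3 is kept, make its condition the absence of documented metastases.

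The cost is SAP wording and one extra sensitivity run, in which a few events will rest on judgement without documentation. The change should be settled before unblinding.

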### 4.2 Study Events Flow Chart

Table A provides a detailed description of the schedule of events.

Table A: Schedule of events

|  | **Screening** | **Treatment** | **Hospital discharge** | **Follow-up at 1, 2, 5 years** |
| --- | --- | --- | --- | --- |
|  | **D-21 to D0** | **D0** | **D8** | **1, 2, 5 years** |
| Written consent | X |  |  |  |
| Inclusion/exclusion criteria | X | X |  |  |
| Randomization |  |  |  |  |
| Baseline data | X |  |  |  |
| Medications | X |  | X | X |
| Histology |  |  | X | X |
| Hospital discharge |  |  | X |  |
| Follow-up at 1 year |  |  |  | X |
| Follow-up at 2 years |  |  |  | X |
| Follow-up at 5 years |  |  |  | X |
| Chemotherapy |  |  | X | X |
| Radiotherapy |  |  | X | X |
| Chronic pain |  |  |  | X |
| Locoregional recurrence assessment |  |  |  | X |
| Distant metastases |  |  |  | X |
| Tumor biomarkers |  |  |  | X |
| Cardiovascular assessment |  | X | X | X |
| Gastro-intestinal assessment |  | X | X |  |
| Blood loss |  | X | X |  |
| Serious Adverse Event |  | X | X |  |
| Death information | X | X | X | X |
| Unblinding |  | X |  |  |
| Screening Log | X |  |  |  |

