### 6.1 Full Analysis Set

The Full Analysis Set (FAS) population is defined as all subjects who have been randomized into the study, whether they actually received treatment or not. Subjects will be analyzed according to the treatment group to which they were randomized. This corresponds to the intent-to-treat (ITT) principle. The FAS population will be the set used for all the efficacy analyses, unless otherwise specified.

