### 7.3 Visit Windows

Tumor assessments will be followed at least every year, according to standard practice.

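### Tables 1–3 of the SAP censor documented recurrences, metastases and deaths after a single missed assessment, and censor at surgery any patient without a baseline assessment, contradicting the endpoint definitions and the tables' own event rows

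*SAP*

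**What the plan says.** In the SAP section Efficacy Variables, DFS is "defined as the time from surgery to the date of disease recurrence/death from any cause". LFS and MFS likewise count death from any cause. Table 2 treats a documented recurrence, and a death before recurrence, as events. The programming note below it takes DFS events from CRF 20, 30 or 99, with no exception for missed visits.

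A later row of Table 2 censors "Death or recurrence after one or more missed scheduled assessments" at the last tumor assessment. Table 1 has "Death or locoregional recurrence after one or more missed scheduled assessments" and Table 3 has "Death or metastases after one or more missed scheduled assessments", with the same consequence. All three tables also contain "No baseline assessments", with censoring on the date of surgery. In Table 2, patients without recurrence at the data cut-off are censored at their last tumor assessment, whatever visits they missed before it.

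On the schedule, Section 7.3 says "Tumor assessments will be followed at least every year, according to standard practice", whereas Table A in Section 4.2 has "Follow-up at 1, 2, 5 years". Section 6.1 defines the Full Analysis Set as "all subjects who have been randomized into the study, whether they actually received treatment or not" and equates it with intention to treat.

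**The concern.** A recurrence or death after a missed visit fits two rows of the same table, one making it an event and the other a censoring. The SAP does not say which row prevails, so two programmers could build different primary datasets. The same death is always an OS event but may be censored for DFS.

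If the censoring row prevails, censoring depends on the outcome: a missed visit costs a patient nothing unless an event follows. One miss is enough, and because visits are a year or more apart, a long stretch of follow-up can be discarded with the event. A patient censored at surgery stays in the Full Analysis Set by name but contributes no outcome.

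This decides which events enter the primary log-rank test. The only other primary analysis planned in Section 10.9.1 is a per-protocol repeat, which would not show what the rule removed.

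**Working it through.** **1. Two patients under the rule (Table A visits).** Both attend year 1 and miss year 2. The first has a documented recurrence at 2.5 years; Table 2's missed-visit row censors that patient at year 1. The second attends year 5 without recurrence and is censored at year 5. They missed the same visit, but only the patient with the bad outcome loses information.

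**2. Share of DFS events lost.** The SAP gives no event rate or attendance rate. Assumptions: constant hazard, 25% events at 2 years, and each visit missed at random with probability m = 5%, 10% or 20%.

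Hazard: λ = −ln(0.75)/2 = 0.1438 per year. Event-free proportions: S(1) = 0.8660, S(2) = 0.7500, S(3) = 0.6495, S(4) = 0.5625, S(5) = 0.4871.

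*To 2 years.* Only the year-1 visit can be missed before an event, so every reading gives the same answer:
m × (0.8660 − 0.7500)/0.25 = 0.464m, that is 2.3% / 4.6% / 9.3%.

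*To 5 years, visits at 1, 2 and 5 years.* Total event probability is 1 − 0.4871 = 0.5129, with 0.1160 falling in years 1–2 and 0.2629 in years 2–5.
- Only a miss just before the event counts: m × (0.1160 + 0.2629)/0.5129 = 0.739m, that is 3.7% / 7.4% / 14.8%.
- Any earlier miss counts: [0.1160m + 0.2629(1 − (1 − m)²)]/0.5129, that is 6.1% / 12.0% / 23.0%.

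*To 5 years, yearly visits, any earlier miss.* Weight the interval after the k-th visit by 1 − (1 − m)^k. The intervals carry 0.1160, 0.1005, 0.0870 and 0.0754, which gives 8.2% / 15.6% / 28.5%.

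**3. Effect on power.** Section 4.5 gives 200 patients for a 33% reduction, 5% type I error and 80% power. Taking HR 0.67 and a two-sided test (neither is stated):
- Schoenfeld: 4(1.960 + 0.842)²/(ln 0.67)² = 195.8, so 196 events.
- Freedman: (1.67/0.33)² × (1.960 + 0.842)² = 201.0, so 202 events with equal arms.

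The 200 is thus reproduced as a number of events, although the SAP calls it patients. With power = Φ(√(d/4) × 0.4005 − 1.960):

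| Events lost | d | Power |
|---|---|---|
| 0% | 196 | 80.0% |
| 5% | 186.2 | 78.0% |
| 10% | 176.4 | 75.8% |
| 20% | 156.8 | 70.8% |

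If 200 really means patients, and control risk is 30%, the treated risk is 1 − 0.70^0.67 = 0.213 and about 51 events are expected. Power is then 29.9%, falling to 27.4% or 24.9% with 10% or 20% of events lost.

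**4. Effect on estimates.** These come from a simulation of 400,000 patients with yearly visits, 30% control events at 2 years and true HR 0.67. With 10% of visits missed at random and any earlier miss counting, the control event probability at 4.9 years reads 0.529 instead of 0.583, and at 2 years 0.292 instead of 0.300. With equal attendance in the arms the HR stays at 0.64–0.67, even if the visit just before an event is missed three times as often. With a true HR of 1.0 and 20% missed on ketorolac against 10% on placebo, the HR reads 0.96 (only a miss just before the event counts) or 0.89 (any earlier miss counts).

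**The case against.** The best defense is that the trial is double-blind with a single dose, so attendance should be similar in the arms, and the HR then moves little. The primary objective concerns DFS after at least 2 years, where the loss is smallest. Both points stand and limit the size. They do not remove the contradictory rows or the dependence on outcome, and follow-up of at least 2 years may run longer.

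A reader might infer several stronger things that the document does not support:

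- *That every event after year 3 is lost even with perfect attendance.* This needs years 3 and 4 to be scheduled, as in Section 7.3, and yet never assessed, as in Table A. Under either schedule alone, perfect attendance loses nothing.
- *That the no-baseline row censors every patient on day 1*, since Table A places recurrence assessment only at follow-up. But Table A has baseline data at screening, and Section 7.1 defines a baseline value. The term is undefined in the censoring tables, and the row may apply to few patients or none.
- *That the missed-visit row breaks the Full Analysis Set.* Section 6.1 fixes who is analyzed and in which arm, and these patients stay in. That argument fits only the no-baseline row.
- *That the primary comparison is biased.* This requires unequal attendance, for which the document gives no evidence.

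**Conclusion.** The censoring rows are wrong as written and need to be settled before unblinding, because they decide which events enter the primary test. On the stated assumptions, about 2% / 5% / 9% of DFS events to 2 years are lost at 5% / 10% / 20% missed visits. To 5 years the range is 4–8%, 7–16% and 15–29%, depending on the schedule and on which misses count. Losing 5%, 10% or 20% of 196 events would cost about 2, 4 or 9 percentage points of power; 196 is itself an inference, since the SAP gives no event target. The ordinary harm is overstated DFS and lost power. Bias between arms is possible, but only with unequal attendance. All magnitudes rest on assumed event and attendance rates; the contradiction between rows, and the one-sided removal of bad outcomes if the censoring row prevails, do not.

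**What to change.** In the primary Full Analysis Set analysis, delete the missed-visit row and the no-baseline row from Tables 1, 2 and 3. Count every documented recurrence or metastasis, and every death, on its date, whatever visits were missed. Censor only patients without a documented event, at their last tumor assessment. The missing-date rules of Section 7.4 are a separate matter and are not changed by this.

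Keep missed-visit censoring, if wanted, only as a labelled sensitivity analysis. Before that, reconcile Section 7.3 with Table A so that a scheduled assessment has one meaning, and state whether any earlier miss or only the one just before the event triggers the rule.

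The cost is SAP wording and programming; no new data are needed. Some events will be dated later or less precisely. Deaths known beyond the last assessment will count while event-free time beyond it will not, an asymmetry in the opposite direction. The SAP should state this; the sensitivity analysis can show how much it matters.

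### Event-free patients are censored back at the last tumour assessment while later recurrences and deaths still count, which under a 1, 2 and 5-year schedule biases the curves after year 2 and costs power

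*SAP*

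**What the plan says.** The Efficacy Variables section of the SAP gives three DFS rules in Table 2 that matter here.

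- Event-free at cut-off: "Patients without recurrence as of data cut-off" take the last tumour assessment as their end date and are censored.
- Recurrence between visits: "Recurrence documented between scheduled visits | Date of the 1st assessment of the series of tests that determined recurrence | No".
- Death: "Death during the study before recurrence | Date of death | No".

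A further row censors a death or recurrence that follows a missed scheduled assessment, at the last assessment. Tables 1 (LFS) and 3 (MFS) have the same structure. OS differs: it is censored at the last date the patient was known to be alive.

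The assessment schedule is given twice. Table A in section 4.2 places locoregional and metastasis assessment in the column "Follow-up at 1, 2, 5 years". Section 7.3 says "Tumor assessments will be followed at least every year", following standard practice.

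The primary objective is DFS after at least 2 years of follow-up. No cut-off date is given. The primary test is a log-rank test (10.9.1), and Kaplan-Meier plots are planned for locoregional RFS, DFS, MFS and OS (10.9.2).

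**The concern.** Take two patients, both seen and found well at year 2, with a cut-off at 3.8 years. One recurs at 3.5 years, found between visits. She stays in the risk set until 3.5 years and counts as an event. The other is still well at 3.8 years. If her next assessment is due at year 5, she is censored back at year 2. Whether a patient is at risk between 2 and 3.5 years is therefore decided by what happens to her later. Kaplan-Meier and the log-rank test both assume that this is not so.

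The direction is predictable: event-free time is discarded and event time is kept, so the curve falls too fast after the last common assessment. At stake are the DFS, LFS and MFS curves beyond year 2 and the power of the primary test.

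**Working it through.** **Inputs from the SAP.** 200 patients, 1:1; a 33% reduction, read as hazard ratio (HR) 0.67; log-rank test at 5%, taken as two-sided; visits at 1, 2 and 5 years (Table A) or yearly (7.3); follow-up of at least 2 years.

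**Assumptions, because the SAP gives no figure.** Exponential event times; control event probability at 2 years of 15%, 20%, 25% or 40%; follow-up at cut-off spread uniformly over about 2 to 5 years, or longer; between-visit recurrences known at cut-off unless stated otherwise.

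The plan gives no figure for this point that could be reproduced first.

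**Hand check, visits at 1, 2 and 5 years.** Let follow-up C be uniform on 2.01 to 4.91 years. Nobody has reached year 5, so every event-free patient leaves at year 2 and only those who will have an event before cut-off remain.

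For 25% control events at 2 years, the hazard is λ = −ln(0.75)/2 = 0.1438. With no treatment effect, the number at risk just after year 2 is

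200 × 0.75 × (1 − E[e^(−λ(C−2))]), where E = (e^(−0.1438×0.01) − e^(−0.1438×2.91)) / (0.1438×2.90) = 0.8165.

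This gives 200 × 0.75 × 0.1835 = 27.5. About 150 patients (200 × 0.75) are in fact still event-free then.

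After year 2 the control curve is 0.75 × F(t), where F(t) is the share of observed post-year-2 events that fall after t:

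F(t) = ∫ₜ^4.91 e^(−λu) P(C>u) du ÷ ∫₂^4.91 e^(−λu) P(C>u) du, with P(C>u) = (4.91 − u)/2.90 for u ≥ 2.01 and 1 before that.

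- Year 3: F = 0.390, curve 0.75 × 0.390 = 0.29; true value e^(−3λ) = 0.65.
- Year 4: F = 0.080, curve 0.75 × 0.080 = 0.06; true value e^(−4λ) = 0.56.

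**Simulation.** 1,500 trials per setting (standard error of a 5% rejection rate about 0.006), comparing the SAP rule with censoring event-free patients at cut-off. In the 20% and 40% rows, accrual is uniform over 3 years with cut-off 2 years after the last patient.

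| Control events at 2 y | Visits (years) | Follow-up (years) | 4-year control KM: SAP rule (true) | Power at HR 0.67: SAP rule / cut-off |
| --- | --- | --- | --- | --- |
| 15% | 1, 2, 5 | 2.0–4.9 | 0.07 (0.72) | 0.13 / 0.25 |
| 20% | 1, 2, 5 | 2–5 | 0.08 (0.64) | 0.16 / 0.33 |
| 25% | 1, 2, 5 | 2.0–4.9 | 0.06 (0.56) | 0.19 / 0.38 |
| 40% | 1, 2, 5 | 2–5 | 0.05 (0.36) | 0.31 / 0.53 |
| 15% | yearly | 2.0–4.9 | 0.68 (0.72) | 0.24 / 0.25 |
| 20% | yearly | 2–5 | 0.59 (0.64) | 0.31 / 0.32 |
| 25% | yearly | 2.0–4.9 | 0.50 (0.56) | 0.35 / 0.36 |
| 25% | 1, 2, 5 | 4.0–6.9 | 0.50 (0.56) | 0.43 / 0.49 |
| 25% | 1, 2, 5 | 5.0–7.9 | 0.56 (0.56) | 0.43 / 0.53 |

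Only the contrast within a row matters; the level of power follows from the assumed event rates.

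Other results:
- At a true HR of 0.67, visits at 1, 2 and 5 years and follow-up of 2.0–4.9 years, the estimated HR moves to about 0.76.
- The 2-year estimate is unbiased (0.75 for a true 0.75).
- Type I error under the SAP rule lies between 0.045 and 0.063 in the 15% and 25% settings, and is 0.054 at 20%.
- With yearly visits and 25% events, the curve is nearly right at 3 years (0.63 against 0.65) and breaks down in the last interval (4.5 years: 0.23 against 0.52).
- In the last table row the same fault has moved beyond year 5, which is why power still differs.

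**The case against.** The strongest reply is that the large figures assume a schedule the SAP may not intend. Table 2 says last tumour assessment, without restricting it to scheduled ones, although section 7.4.1 uses that restriction elsewhere. Section 7.3 sets assessments at least yearly. On that reading, patients are censored within about a year of cut-off and power hardly changes. This stands, and it is why the point is conditional. It does not dispose of it: Table A has no year-3 or year-4 column, so it is unclear whether an event-free assessment in those years would be recorded.

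Second, if recurrences also reach the database only at the next visit, events and non-events are equally unknown in the gap. This stands in part. With only half of recurrences dated between visits (25% events, Table A visits, follow-up 2.0–4.9 years), power falls from 0.27 to 0.21 rather than by half. The 4-year curve still collapses to 0.06, and it does so (0.07) when only 30% of post-visit events are captured. In the half-captured case, simply moving censoring to cut-off errs the other way (0.64 against a true 0.56), so any remedy must treat events and event-free status alike.

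Third, the missed-assessment row removes some late events. It does not help for patients who attended every visit.

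A reader might also infer more than the document supports:
- *The log-rank test is invalid.* Both arms follow the same rule and type I error stays near 5%; the harm is attenuation and lost power.
- *The 5-year LFS result is uninterpretable.* A 5-year analysis needs 5-year follow-up, and once all patients have it there is no bias before year 5.
- *Recurrences count at their true date.* They count at the first determining assessment.

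**Conclusion.** The asymmetry is in the text of Tables 1 to 3 and makes censoring depend on outcome. Its size depends on the schedule and the cut-off, neither of which the SAP settles.

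- **Table A visits, many patients between years 2 and 5 at cut-off:** severe. Curves after year 2 are close to meaningless, and up to about half the power is lost.
- **Truly yearly assessments:** small. The 4-year estimate is 4 to 6 points low, power is nearly unchanged, and the curve fails only in its last interval.
- **All patients past year 5:** no bias before year 5; some power is still lost through events after it.

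In every case examined, the 2-year estimate was unbiased or nearly so and type I error was near 5%, so a false-positive primary result is not the worry. These sizes rest on the assumed event rates, exponential times and uniform follow-up. The direction of the bias does not.

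**What to change.** 1. Reconcile section 7.3 with Table A so that one assessment schedule applies, and state the data cut-off.
2. In Tables 1 to 3, replace the event-free row with one symmetric rule: censor at the last date known alive and free of the event, up to cut-off, with disease status updated to cut-off for all patients in the same way as events are ascertained. The OS rule already follows this idea.
3. Where status is not updated to cut-off, count neither recurrences nor deaths beyond the last assessment time that all patients have reached, at least as a sensitivity analysis.
4. In Table 1, the row "Patients still on treatment without PD as of data cut-off" does not fit a single-dose trial; reword it as patients without locoregional recurrence at cut-off. This is a wording correction and adds nothing to the argument above.

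The cost is a few lines of SAP text, made before unblinding, and capture of a last disease-status date for each patient. The downside is that status between visits then rests on routine contact rather than formal assessment. Truncation has its own price: in the 20% setting with no treatment effect, about 24 of 64 events fall after year 2 and would be lost by stopping there.
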